## **Risk factors**

Risk factors will be considered in two groups, of differing levels of priority. The 'List of risk factor variables' table in the Appendix specifies the group to which each variable is assigned.

Group 1 consists of variables that will be included in the statistical model regardless of statistical significance. These include demographic characteristics that it is necessary to include to ensure the model has face validity, and other risk factors suspected on the basis of previous research or subject-matter judgment to be associated with a self-harm outcome.

Group 2 consists of variables likely to show an association with outcomes but which are not required to be included to achieve face validity. The model will use a backwards stepwise selection procedure to determine whether to retain these variables in the model, with Group 1 variables always retained and Group 2 variables sequentially rejected in order of p-value until no group 2 variables remain that have p-values greater than 0.1.

This strategy of risk factor adjustment recognises that the final model must demonstrate face validity, whilst simultaneously allowing the inclusion of additional risk factors if they show an association with outcome variables. The variables are considered in two groups in this way to recognise that a parsimonious model is preferable and easier to use in practice, provided that it has acceptable predictive ability.

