## Study Summary

**Design:** Retrospective multi-centre cohort study.

**Participants:** Male and female prisoners, aged 18+, in selected category A-C prisons in England who have been managed by the Assessment, Care in Custody and Teamwork (ACCT) process in response to concerns of being at risk for self-harm or suicide.

**Data sources:** Three linked data sources: ACCT records, SystmOne medical records and Nomis (a central prison database).

**Study period:** Included participants had ACCTs closed prior to June 2022, with a minimum of three months of follow-up per participant.

**Risk factors:** A range of variables including demographics characteristics, variables indicative of mental health at opening and closure of the ACCT, history of self-harm, variables relating to history of and reasons for incarceration, variables indicative of health status and medication use.

**Primary outcome:** ACCT reopening within 3 months following closure of the ACCT. The target sample size was 750, anticipating that a 20% event rate would yield 150 outcome events within 3 months.

**Outputs:** The main objective is to produce models that estimate outcome probabilities within 3 months, with appropriate measures of predictive accuracy.

These models will be used to obtain scoring systems for the calculation of risk to be used prospectively at the time of ACCT closure.

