Each individual has an 'index ACCT' that defines the time point at which risk factor variables are available, and the closure of this ACCT is interpreted as time 0 for defining subsequent follow-up times. In the case that more than one ACCT from the same individual is available as an index ACCT, the most recent of these that has substantially complete risk factor data will be used in the primary analysis. A sensitivity analysis will be carried out to check that the selection of this index ACCT does not have an undue influence on results.

Covariates that have more than 30% missing data will be excluded. Missing data on covariates with at most 30% missing data will be imputed via multiple imputation (with twenty imputations) using a regression model that uses other risk factors and the outcome variables as explanatory variables (Sterne et al., 2009). Estimates of coefficients in the final prediction rule will be combined across imputations, using standard methodology (Barnard and Rubin, 1999). It is possible that the variable selection procedure would give different sets of variables in different imputations of the data-set; for this reason, the 'RR' method described by Wood et al. (2008) will be used. In this method,

summary estimates are computed by combining information across all imputed data-sets at each stage as part of a single variable selection process.

Internal validation will be assessed using bootstrapping to assess the predictive accuracy of the model (Harrell et al., 1996). Predictive accuracy will be summarised using several summary measures, including the concordance index (Harrell et al., 1982) and estimates of sensitivity and specificity corresponding to different values of a risk threshold. The proportions of predicted and observed events at different levels of predicted probability will be compared using a calibration plot.

Data will be collected from multiple prison sites (expected to be 6 different prisons in England). The main model will be fitted using data from all sites combined. Performance measures will also be presented stratified by site in order to identify whether there are any major between-site differences that may impact on performance in an external validation sample.

This analysis plan does not incorporate an external validation step as it is planned to conduct a separate external validation substudy, using data from a different selection of prisons, concurrently with the analysis in the model development stage.

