| First reception at current prison                              | Nomis  | -     | Date                    | Used to calculate time between reception at current prison and ACCT opening (see below)                                                                                   |
| Follow-up ACCT reopening                                       | Nomis  | -     | Date                    | Primary outcome is time between ACCT closure and first subsequent ACCT reopening                                                                                          |
|                                                                |        |       |                         |                                                                                                                                                                           |
| Risk factor variables                                   |        |       |                         |                                                                                                                                                                           |
| Sex                                                            | -      | 1     | Binary                  | Prisons are single-sex so prison site indicates sex of prisoner. Coded as Male or Female.                                                                                 |
| Reason for ACCT opening                                        | ACCT   | 1     | Categorical             | Categorised as self-harm; threat of self-harm; low mood (including all other reasons for ACCT opening)                                                                    |
| Method of self-harm                                            | ACCT   | 2     | Categorical             | Categorised as cutting; strangulation; overdose; other method; not applicable (no self-harm)                                                                              |
| Current suicidal thoughts or intentions                        | ACCT   | 1     | Binary                  | At ACCT opening. Categorised as Yes or No.                                                                                                                                |

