| Previous ACCT within 6 months prior to ACCT opening | Nomis    | 1 | Binary                    | Categorised as Yes or No                                                                                                                                    |
| Age                                                 | SystmOne | 1 | Continuous                | Measured at time of ACCT closure                                                                                                                            |
| Ethnicity                                           | SystmOne | 2 | Binary                    | Categorised as non-white or white                                                                                                                           |
| Marital status                                      | SystmOne | 2 | Binary                    | Categorised as 'Currently single' (single / widowed / divorced / separated) or 'Not currently single'                                                       |
| Current medication                                  | SystmOne | 2 | Categorical               | Categorised by medication class (antidepressants, ADHD medication, antipsychotics, mood stabilisers, opioids, sleepers, pain relief).                       |
| Previous psychotropic medication in last 6 months   | SystmOne | 2 | Binary                    | Categorised as Yes or No                                                                                                                                    |

|                                                                                                                                                                                                                      |          |   |             |                                                                                                                                                                                                                                                                                                                                                       |

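### About 45 candidate parameters are screened by backward elimination on about 150 events with no shrinkage specified, so predicted probabilities are expected to be too extreme

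*SAP*

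**What the plan says.** - **Size.** Study Summary: "The target sample size was 750, anticipating that a 20% event rate would yield 150 outcome events within 3 months".
- **Forced variables.** Risk factors: "Group 1 consists of variables that will be included in the statistical model regardless of statistical significance".
- **Selection.** Risk factors: the rest are eliminated backwards, with "Group 2 variables sequentially rejected in order of p-value until no group 2 variables remain that have p-values greater than 0.1".
- **Final coefficients.** Section 2: "Estimates of coefficients in the final prediction rule will be combined across imputations". The RR method is named so that one selection process runs across all 20 imputed data sets. Shrinkage, penalisation, a calibration slope and recalibration are not mentioned anywhere.
- **Validation.** Section 2: "Internal validation will be assessed using bootstrapping to assess the predictive accuracy of the model", summarised by the concordance index and by sensitivity and specificity, with a calibration plot. The bootstrap is described by reference to a methods paper. External validation is left to a separate substudy that runs alongside model development.
- **Use.** The Study Summary makes 3-month outcome probabilities the main objective and derives from them a scoring system for prospective use at ACCT closure. Section 2 lets the distribution of the risk estimates guide the choice of a probability threshold for high risk.

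**The concern.** Overfitting is driven by the number of parameters screened, not by the number that survive, so a short final model is no protection. With few events per candidate, elimination at p > 0.1 keeps effects that happen to look large in this sample. Coefficients carried forward without correction then spread the predictions too widely: high risks are overstated and low risks understated.

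This bears directly on the study's main product, because the tool is meant to report a probability. At the top, stated risks would be higher than those that occur. At the bottom, some prisoners would be described as safer than they are.

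**Working it through.** **1. The plan's own figure.** 750 × 0.20 = 150 events. This reproduces.

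**2. Candidate parameters, from the Appendix 1 table.** Count categories minus one, and one for each binary or linear variable.

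- Group 1: sex 1; reason for opening 2 ("Categorised as self-harm; threat of self-harm; low mood (including all other reasons for ACCT opening"); suicidal thoughts 1; previous ACCT 1; age 1. Total 6.
- Group 2:
  - method of self-harm 4 ("Categorised as cutting; strangulation; overdose; other method; not applicable (no self-harm");
  - case reviews, first-review risk level, CAREMAP, GP referral, mental health referral, friends/family support: 6;
  - the nine Nomis rows from drug screen to IDTS/DARS referral: 9;
  - ethnicity 1, marital status 1, medication 7 ("Categorised by medication class (antidepressants, ADHD medication, antipsychotics, mood stabilisers, opioids, sleepers, pain relief"), previous psychotropic medication 1: 10;
  - liver enzymes, primary care, mental health services: 3;
  - previous self-harm 1, diagnoses 4, length of ACCT 2: 7.
  - Total 4 + 6 + 9 + 10 + 3 + 7 = 39.

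All candidates: 6 + 39 = 45. Counting medication once gives 45 − 6 = 39. The count is 44 if the not-applicable level of method is aliased with reason for opening, and 48 if the three variables that may be categorical become three-level. The post-closure review variable is left out because it is not available at closure.

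Events per candidate parameter: 150/45 = 3.3; 150/39 = 3.8; 150/48 = 3.1. If the rule dropping covariates with more than 30% missing data left 30 parameters (an assumption), 150/30 = 5.0.

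**3. Expected shrinkage factor S.** The standard formula, treating the 3-month event as binary, is S = 1 + p / (n ln(1 − R²/S)), with n = 750. The largest possible Cox-Snell R² at 20% events is 1 − (0.2^0.2 × 0.8^0.8)² = 0.632. The SAP gives no R², so 10% to 25% of that maximum is assumed.

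| Parameters | 10% | 15% | 20% | 25% |
|---|---|---|---|---|
| 45 | 0.53 | 0.63 | 0.70 | 0.75 |
| 39 | 0.56 | 0.66 | 0.73 | 0.77 |
| 30 | 0.63 | 0.72 | 0.78 | 0.82 |

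Example: 45 parameters at 15% gives R² = 0.0949. With S = 0.631, ln(1 − 0.0949/0.631) = −0.163, and 1 − 45/(750 × 0.163) = 0.63.

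For S of at least 0.9 without shrinkage, 750 prisoners support about 5 to 14 candidates. Conversely, 45 candidates need about 2,330 to 6,177 prisoners (466 to 1,236 events).

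**4. Simulation of the selection rule.** Setup: Cox model, 750 subjects, about 150 events, 45 parameters with 6 forced in, elimination at p > 0.1, 200 replicates per scenario, validation in 20,000 subjects. True C, number of real predictors, prevalences and correlation are assumed.

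| Scenario | Median slope | Top decile, predicted / observed | Bottom decile, predicted / observed |
|---|---|---|---|
| C 0.65, 15 real | 0.48 | 45% / 32% | 6% / 12% |
| C 0.70, 15 real | 0.60 | 53% / 39% | 4% / 8% |
| C 0.70, all 45 weak | 0.50 | 53% / 36% | 4% / 9% |
| C 0.75, 15 real | 0.74 | 60% / 49% | 3% / 5% |

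The slope was below 0.9 in 94% to 100% of replicates. Apparent C exceeded validated C by 0.06 to 0.11.

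**5. What a slope means for one prisoner.** Take the 20% average risk as reference: cumulative hazard −ln 0.8 = 0.223. A stated 50% has cumulative hazard 0.693, so its log hazard ratio is ln(0.693/0.223) = 1.13.

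- Slope 0.5: 1.13 × 0.5 = 0.567; risk = 1 − exp(−0.223 × e^0.567) = 33%.
- Slope 0.75: 1.13 × 0.75 = 0.850; risk = 1 − exp(−0.223 × e^0.850) = 41%.

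**6. Does shrinkage help?** Applying a bootstrap slope, with selection repeated in each resample (25 data sets × 30 resamples, 15 real predictors), raised the mean validation slope from 0.49, 0.64 and 0.69 to 0.84, 0.95 and 0.97 at true C 0.65, 0.70 and 0.75. At C 0.70 the top decile was then predicted at 42.5% against 40.7% observed.

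**The case against.** **The SAP does not say the coefficients are unshrunk.** This stands as a point of wording: the reading comes from silence. But the SAP describes selection and pooling in detail and gives no other treatment of the coefficients, so carrying it out as written leaves them uncorrected.

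**The bootstrap is specified by a cited paper.** A reader might infer that only the selected model will be resampled, which would understate the optimism. The SAP does not say so, and the cited method may cover repeated selection. What can be said is that the SAP's own text leaves this open. Even a full optimism correction of the accuracy measures would leave the score's probabilities unchanged.

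**There are other safeguards.** The 30% missingness rule may shorten the list, the calibration plot compares predicted with observed events, and external validation may detect miscalibration. All true. But 30 parameters still give 0.63 to 0.82, and none of these steps is planned to correct the score.

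**Wrong prisoners flagged?** A reader might infer that missing shrinkage makes the tool flag the wrong people. The documents do not support that. Uniform shrinkage with a re-estimated baseline keeps the order of risks, so a cut-off placed at a given fraction of prisoners flags the same ones, with the same C-index, sensitivity and specificity. Only absolute risks and cut-offs fixed as probabilities are affected.

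**The true signal is unknown.** This limits confidence in the size. The direction was the same in every scenario examined.

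**Conclusion.** The point holds as an expectation about absolute risk. With 39 to 45 candidate parameters, 150 events and no correction specified, the slope in new data is expected to be roughly 0.5 to 0.75 at 45 parameters, the range covered by both the formula and the simulation. No assumed scenario reached an expected slope of 0.9.

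The size rests on an assumed R² of 10% to 25% of maximum, on the simulation's assumptions, and on 150 events being reached. Non-linear terms or the time-varying effects that section 2 allows would add parameters, and censoring at release before 3 months could reduce events; either would lower the events per parameter. It would go too far to say that the probabilities will certainly be too extreme by a stated amount, or that the SAP has ruled shrinkage out.

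**What to change.** In section 2, add four statements:

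1. The full RR backward elimination, with Group 1 forced in, is repeated in every bootstrap sample.
2. The final coefficients are multiplied by the optimism-corrected calibration slope and the baseline hazard is then re-estimated. Alternatively, a penalised Cox model is fitted with Group 1 forced in.
3. The scoring system is built from the shrunk coefficients.
4. The optimism-corrected calibration slope, C-index, sensitivity and specificity are reported.

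It would also help to state the number of candidate parameters beside the 150 events.

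Cost: SAP wording and more computing, because the selection is rerun for each bootstrap sample across 20 imputations. No new data are needed. Headline accuracy will look less favourable, which comes from the optimism correction and not from the shrinkage. Uniform shrinkage may not fully restore calibration if the true signal is weak: in the check it reached a slope of 0.84 at true C 0.65.

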## **Appendix 1: List of variables and data sources**

Sex (based on single-sex prison in which prisoner is incarcerated)

### ACCT records

Date ACCT open & closed

Reason for ACCT

Method of self-harm

Current suicidal thoughts or intentions

Number of case reviews

Level of risk at first review

CAREMAP actions completed

Referred to GP or mental health services

Friends/family support

Date of post-closure review (ACCT v5 the typical post-closure period is 7 days, ACCT v6 is 6 weeks)

Issues resolved in post-closure

### Nomis

Expected release date

Date of first reception for this period in custody

Drug screen

Index offence

Number of transfers in current prison term

First time in custody

Dates of previous and follow-up self-harm incidents

IDTS (Integrated Drug Treatment System) / DARS (Drug and Alcohol Rehabilitation Services) referral

### SystemOne

Age

Ethnicity

Marital status

Current medication

Previous psychotropic medication in last 6 months

Abnormal liver function enzymes

Engaging with primary care or prison mental health services

Previous self-harm at reception screening

Previous diagnoses

| Variable                                                       | Source | Group | Type                    | Notes                                                                                                                                                                     |
|----------------------------------------------------------------|--------|-------|-------------------------|---------------------------------------------------------------------------------------------------------------------------------------------------------------------------|
| Date variables used to define risk factors and outcomes |        |       |                         |                                                                                                                                                                           |
| Date open & closed                                             | ACCT   | -     | Date                    | Used to define length of ACCT (see below)                                                                                                                                 |
| Dates of previous ACCTs                                        | Nomis  | -     | Date                    | Used to calculate measures of history of ACCT opening before the index ACCT                                                                                               |
| Expected release date                                          | Nomis  | -     | Date                    | Used to define time until expected release (see below)                                                                                                                    |
| First reception for this period in custody                     | Nomis  | -     | Date                    | Used to calculate time between reception in custody and ACCT opening (see below)                                                                                          |
| First reception at current prison                              | Nomis  | -     | Date                    | Used to calculate time between reception at current prison and ACCT opening (see below)                                                                                   |
| Follow-up ACCT reopening                                       | Nomis  | -     | Date                    | Primary outcome is time between ACCT closure and first subsequent ACCT reopening                                                                                          |
|                                                                |        |       |                         |                                                                                                                                                                           |
| Risk factor variables                                   |        |       |                         |                                                                                                                                                                           |
| Sex                                                            | -      | 1     | Binary                  | Prisons are single-sex so prison site indicates sex of prisoner. Coded as Male or Female.                                                                                 |
| Reason for ACCT opening                                        | ACCT   | 1     | Categorical             | Categorised as self-harm; threat of self-harm; low mood (including all other reasons for ACCT opening)                                                                    |
| Method of self-harm                                            | ACCT   | 2     | Categorical             | Categorised as cutting; strangulation; overdose; other method; not applicable (no self-harm)                                                                              |
| Current suicidal thoughts or intentions                        | ACCT   | 1     | Binary                  | At ACCT opening. Categorised as Yes or No.                                                                                                                                |
| Number of case reviews                                         | ACCT   | 2     | Discrete or categorical |                                                                                                                                                                           |
| Level of risk at first case review                             | ACCT   | 2     | Binary                  | Refers to first case review after ACCT opening. Categorised as 'High' or 'Low' (with the category 'Raised' used in one version of the ACCT document grouped with 'High'). |
| CAREMAP actions completed                                      | ACCT   | 2     | Binary                  | Refers to first case review after ACCT opening.                                                                                                                           |

|                                                     |          |   |                           |                                                                                                                                                             |
|-----------------------------------------------------|----------|---|---------------------------|-------------------------------------------------------------------------------------------------------------------------------------------------------------|
|                                                     |          |   |                           | Categorised as Yes or No.                                                                                                                                   |
| Referred to GP                                      | ACCT     | 2 | Binary                    | Categorised as Yes or No                                                                                                                                    |
| Referred to mental health                           | ACCT     | 2 | Binary                    | Categorised as Yes or No                                                                                                                                    |
| Friends/family support                              | ACCT     | 2 | Binary                    | Categorised as Yes or No                                                                                                                                    |
| Drug screen                                         | Nomis    | 2 | Binary                    | At start of custody.
Categorised as Yes (positive) or No (no test recorded).                                                                             |
| Index offence                                       | Nomis    | 2 | Binary                    | Categorised as 'Violent' or 'Non-violent' index offence                                                                                                     |
| Number of transfers in current prison term          | Nomis    | 2 | Discrete or categorical   |                                                                                                                                                             |
| Time until expected release                         | Nomis    | 2 | Continuous                | Calculated as time between ACCT closure date and expected release date. If included in model, must be used alongside life sentence and IPP variables below. |
| Life sentence                                       | Nomis    | 2 | Binary                    | Categorised as Yes or No                                                                                                                                    |
| IPP (imprisonment for public protection) sentence   | Nomis    | 2 | Binary                    | Also includes other non-life sentences for which an expected release date is not applicable. Categorised as Yes or No.                                      |
| First time in custody                               | Nomis    | 2 | Binary                    | Categorised as Yes or No                                                                                                                                    |
| Time since first reception in custody               | Nomis    | 2 | Continuous or categorical |                                                                                                                                                             |
| IDTS/DARS referral                                  | Nomis    | 2 | Binary                    | Integrated Drug Treatment System or Drug and Alcohol Rehabilitation Services referral. Categorised as Yes or No.                                            |
| Previous ACCT within 6 months prior to ACCT opening | Nomis    | 1 | Binary                    | Categorised as Yes or No                                                                                                                                    |
| Age                                                 | SystmOne | 1 | Continuous                | Measured at time of ACCT closure                                                                                                                            |
| Ethnicity                                           | SystmOne | 2 | Binary                    | Categorised as non-white or white                                                                                                                           |
| Marital status                                      | SystmOne | 2 | Binary                    | Categorised as 'Currently single' (single / widowed / divorced / separated) or 'Not currently single'                                                       |
| Current medication                                  | SystmOne | 2 | Categorical               | Categorised by medication class (antidepressants, ADHD medication, antipsychotics, mood stabilisers, opioids, sleepers, pain relief).                       |
| Previous psychotropic medication in last 6 months   | SystmOne | 2 | Binary                    | Categorised as Yes or No                                                                                                                                    |

|                                                                                                                                                                                                                      |          |   |             |                                                                                                                                                                                                                                                                                                                                                       |
|----------------------------------------------------------------------------------------------------------------------------------------------------------------------------------------------------------------------|----------|---|-------------|-------------------------------------------------------------------------------------------------------------------------------------------------------------------------------------------------------------------------------------------------------------------------------------------------------------------------------------------------------|
| Abnormal liver function enzymes                                                                                                                                                                                      | SystmOne | 2 | Binary      | Categorised as Yes or No                                                                                                                                                                                                                                                                                                                              |
| Engaging with primary care                                                                                                                                                                                           | SystmOne | 2 | Binary      | Categorised as Yes or No                                                                                                                                                                                                                                                                                                                              |
| Engaging with mental health services (MHIRT)                                                                                                                                                                         | SystmOne | 2 | Binary      | Categorised as Yes or No                                                                                                                                                                                                                                                                                                                              |
| Previous self-harm at reception screening                                                                                                                                                                            | SystmOne | 2 | Binary      | Categorised as Yes or No                                                                                                                                                                                                                                                                                                                              |
| Previous diagnoses: 
 
• Learning disability or neurodevelopmental disorder
 
• Mental illness
 
• Substance misuse
 
• Chronic physical illness
 
 | SystmOne | 2 | Binary      | Each categorised as Yes or No
Learning disability or neurodevelopmental disorder and chronic physical illness variables refer to lifetime diagnosis (any time before ACCT closure).
The other diagnoses refer to diagnoses made within 1 year prior to ACCT closure.
Substance misuse includes both alcohol and drug/other substance misuse. |
| Length of ACCT (days)                                                                                                                                                                                                | ACCT     | 2 | Categorical | 0-1, 2-9, 10+                                                                                                                                                                                                                                                                                                                                         |
| Variables available at post-ACCT review                                                                                                                                                                       |          |   |             |                                                                                                                                                                                                                                                                                                                                                       |
| Date of post-closure review                                                                                                                                                                                          | ACCT     | - | Date        | Date of post-closure review. For ACCT v5 the usual post-closure period is 7 days, for ACCT v6 is 6 weeks.                                                                                                                                                                                                                                             |
| Issues resolved in post-closure review                                                                                                                                                                               | ACCT     | 2 | Binary      | Refers to post-ACCT closure review. Categorised as Yes or No (with 'Partially' classified as No).                                                                                                                                                                                                                                                     |
